## Methods

### Strategy of the Study

The objective of the study is to evaluate 3 different interventions aimed at improving adherence and retention to ART therapy among HIV-positive women through engagement with their life partner. The interventions are (1) testing peer-to-peer counseling and community-level health education sessions delivered by men, *male champions*; (2) opening the facility once a month, only for men, *special day*; and (3) providing incentive to all women accompanied by their partners at the facility, *nudge* or *incentive*.

The different interventions to be implemented and evaluated in the research plan are designed to assess male involvement at the following levels, as depicted in the model represented in Figure 1. The activities that act on the individual and interpersonal or at the social network level common to past studies are transversal to all 3 interventions. At the individual level, both women and their male partners will receive educational content on the importance of retention and adherence to treatments, but also messages that contradict stereotypes and false myths related to masculinity, health, and gender violence. With regard to the interpersonal or social network level, all interventions will include support activities that are aimed at the family (couples counseling).

*Intervention 1* (*Male Champions*) will act at the community level, providing educational interventions that are aimed at territorial communities and religious groups.*Intervention 2* (*Special Day*) will act at the health system level, delivering activities based on health facilities that are aimed at reshaping the clinic as male-friendly.*Intervention 3* (*Nudge*) will also act at the structural level by providing incentives to support the cost of transportation and other costs that reduce a male partner’s ability to access the service.

The study has 3 phases: preintervention (baseline), intervention, and postintervention analyses, as shown in Figure 2.

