### Setting and Participants

The study was performed in Malawi within the Disease Relief through Excellent and Advanced Means (DREAM) program. DREAM is a health program managed by the Community of Sant’Egidio in 11 African countries [28]. The program delivers a number of health services: HIV care, HIV PMTCT, malnutrition prevention and control, care of noncommunicable diseases, tuberculosis diagnosis and treatment, cervical cancer screening, and treatment of early lesions [29-33]. The DREAM program in Malawi runs 13 health centers and 3 laboratories in collaboration with the Ministry of Health. Currently, the DREAM program in Malawi has cared for over 86,000 patients and assisted over 12,000 HIV-positive pregnant women in the prenatal care and delivery of HIV-uninfected babies. In addition, the DREAM program aims to address health inequalities related to HIV, along with barriers experienced by women in accessing services. For this purpose, an expert client model aimed at improving retention in care and facilitating the inclusion of social aspects in the clinical process was launched [34]. However, activities involving male partners with the goal of improving access of their partners to services have never been tested in this model.

Given the limited resources available for the study and the practical difficulties related to the disadvantaged context in which the study was conducted, sample size calculations and criteria for assigning interventions were based on a pragmatic approach. The number of selected clusters is limited to 4, one for each intervention plus a cluster where no intervention will be performed as a control arm. The number of participants enrolled for data collection is given by the number of patients attending the selected clinical centers during the pre- and postintervention phases. Therefore, the main unit of analysis of the study is the cluster, which is the clinical center. Thus, the interventions will target each health facility.

The following criteria were followed to select the 4 centers included in the intervention:

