^a^DREAM: Disease Relief through Excellent and Advanced Means.

These strategies will be implemented according to standard clinical practices in Malawi with some modifications based on the international experiences described in the literature.

The *male champion* is a figure present in a few settings that conducts home visits with men and couples and follows up with men who did not accompany their partners to ANC visits [39]. Usually, this role is covered by the female expert clients, namely HIV-positive patients working in the organization as volunteers after appropriate training. Some men among patients who are receiving treatment will be identified and trained to cover this role [40]. The intervention called *male champion* aims to change the beliefs and attitudes of men, not intervening directly on individuals but upon entire communities and particularly involving community leaders.The *special day* is a practice that is becoming increasingly common to facilitate access to health facilities by vulnerable groups such as adolescents [41,42]. In this study, we target men. The special day takes place with an extraordinary opening of the clinical center once a month on a prefestive day (Saturday). During this day, access will be reserved exclusively for men, including those who are not on treatment for HIV. The center will offer free health promotion services to all participants. This intervention aims to remove the attitude linked to beliefs regarding masculinity, in which the male partners see access to health centers as an activity suitable only for women. The special day aims to make the clinical center more male-friendly and therefore attempts to overcome the social pressure that pushes men to have only sporadic attendance.The intervention based on the use of incentives (*nudge*) [43] to men who follow the prevention and treatment program aims to evaluate whether this action is effective in guiding behavior change toward the test, treatment, involvement, and adherence to therapy approach. The intervention defined as *budget* aims to remove the obstacles of a structural or a material nature, which supports the costs related to transportation to health care facilities and time taken away from work through a noneconomic incentive.

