### Outcomes and Statistical Methods

The outcomes will be divided into 2 levels: (1) evaluation of the variations in retention in care and women's adherence to therapeutic protocols (primary outcome) and (2) assessment of the variations in male involvement (intermediate outcome).

Retention in care and adherence to treatment protocols are primary outcomes. Retention in care will be measured as the cumulative proportion of dropouts from the treatment program at 6 months, 1 year, and 2 years (excluding patients transferred to another center or those who died). Adherence will be measured through the following indicators: (1) the cumulative proportion of medical appointments missed in a month in the center; (2) the cumulative proportion of appointments for drug delivery missed in a month in the center; (3) the cumulative proportion of women who suppressed viral load; and (4) the cumulative proportion of women with a suppressed viral load that has a rebound in viremia.

To evaluate the level of male involvement in the health of female partners (intermediate outcome), a dedicated questionnaire will be delivered to female partners at baseline (preintervention) and in the postintervention phase. The survey measures the following outcomes related to male involvement: (1) proportion of women accompanied by partners at the facility after receiving an invitation card; (2) proportion of men accepting HIV testing and counseling (if not yet received in the last 6 months); (3) level of partner involvement in the care process measured through a score scale based on health practices reported by the female partners; and (4) level of gender-based violence in the family measured through a score scale based on violent or negative practices reported by female partners.

Some indicators will be collected to monitor the delivery of the intervention and possibly evaluate correlations with the dose of delivery of the 3 interventions, as outlined in Textbox 1.

The primary and secondary indicators of effectiveness are the same for all interventions, hence making it possible to assess the differential impact of the community, health system, and structural-level interventions, particularly with respect to interventions based only on individual and interpersonal levels. These interventions will be compared with the usual services offered at the fourth center.

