## Discussion

### Study Strengths

This study aims to assess interventions targeted at enhancing the involvement of males in women antenatal health care in Malawi. Male involvement in prenatal care is still one of the lowest in the world in Malawi, ranging from 3.2% to 23% [27]. There are multiple reasons for the limited role of male partners in women’s health initiatives. Instead of addressing singular factors supposed to directly cause limited male involvement, the approach of our study is based on an ecological model [17]. The decision to base interventions on a theoretical framework is one of the strengths of this study. In fact, a theory-based approach allows us to better understand the reasons for failure or success of an intervention, develop better strategies, and evaluate their external validity [16,50]. In particular, the ecological model was chosen for this study because it considers not only the beneficiaries (HIV-positive women and their partners) and ART adherence as done in other studies [15] but also the social context that can facilitate or hinder the adoption of healthy practices, namely retention in care and adherence to therapy for HIV PMTCT. All the interventions being evaluated act on individual and interpersonal elements, through couple health education. In addition, each intervention addresses other elements such as the health structure, the community, or the structural level linked to transportation costs. This design allows us to understand how the different levels affect behaviors within the target group and, therefore, health outcomes. Another strength of these interventions is the implementation of these activities in a real-life setting, with the use of personnel already active in the center. This is a significant strength of this study, as it provides reproducible information to other sites.

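### The effect of a single ecological level over individual and interpersonal activities alone cannot be estimated, because no center delivers those activities alone

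*Protocol article*

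**What the plan says.** Under Outcomes and Statistical Methods, the article argues that the effectiveness indicators are the same for all interventions, "hence making it possible to assess the differential impact of the community, health system, and structural-level interventions", and adds "particularly with respect to interventions based only on individual and interpersonal levels". The next sentence names the comparator: "These interventions will be compared with the usual services offered at the fourth center".

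The arms are fixed under Setting and Participants: "The number of selected clusters is limited to 4, one for each intervention plus a cluster where no intervention will be performed as a control". Strategy of the Study says that the individual-level and interpersonal activities "are transversal to all 3 interventions", and assigns one further level to each: community for male champions, health system for special day, structural for nudge. Table 1 shows the same pattern, listing both shared levels plus one other in every intervention arm.

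Study Strengths returns to the claim: "This design allows us to understand how the different levels affect behaviors within the target group".

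**The concern.** The statement about differential impact names a reference, namely interventions confined to the individual and interpersonal levels. To estimate what a further level adds to that reference, the study must observe the reference somewhere. It observes three bundles and one center with usual services. Measuring the same indicators everywhere makes the centers comparable in what is recorded, but it does not supply a condition that no center receives.

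What is at stake is attribution. If a package does better than usual services, the text as written would allow a conclusion about the ecological level that the package adds, although the shared education and counseling may account for some or all of the difference. The article wants the theory to explain why an intervention works and whether it transfers to other settings, so this is a conclusion that readers would want to draw.

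**Working it through.** The article gives no power or effect figure on this point, and none is needed. The question is whether the quantities can be estimated from the arms that exist.

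**Inputs.** Four centers, one per intervention plus a control (Setting and Participants). Shared individual and interpersonal activities in all three interventions, plus one further level each (Strategy of the Study, Table 1). Usual services as comparator (Outcomes and Statistical Methods).

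**Step 1: contrasts against control.** Let B be the effect of the shared bundle, and C, H and S the added effects of the community, health-system and structural levels. Under additivity, the change relative to control is:

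- control: 0
- male champions: B + C
- special day: B + H
- nudge: B + S

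That is three non-zero equations in four unknowns; the design matrix has rank 3 of 4.

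**Step 2: what is estimable.** For any number k, replacing B by B + k and C, H, S by C − k, H − k, S − k leaves all three sums unchanged. Hence none of B, C, H or S is estimable. The package effects B + C, B + H and B + S are. So are the differences, for example (B + C) − (B + H) = C − H, and likewise C − S and H − S, provided that B is the same in all arms.

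**Step 3: if the shared bundle differs by arm.** With a separate B for each arm there are 3 + 3 = 6 unknowns, still at rank 3. The contrast between male champions and special day then equals C − H plus the difference between their two bundles, so C − H is not estimable.

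**Step 4: does the text settle that B is common?** It does not:

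- Strategy of the Study promises couples counseling in all interventions. Table 1 itemizes it only for nudge.
- The Interventions section says male champions work on whole communities and do not intervene directly on individuals. Table 1 lists individual counseling for men in that arm.
- The Interventions section describes three different approaches to delivering the educational content.

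**Step 5: before-and-after data.** Four centers at two times give 8 cells. Center effects (4), a period effect (1) and B, C, H, S (4) make 9 parameters; the rank is 8, with 8 − 8 = 0 residual degrees of freedom. The baseline phase therefore does not resolve the problem, and any center-specific change over time is absorbed into the package contrast.

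**Step 6: a hypothetical bundle-only arm.** A fifth arm would raise the rank in Step 1 to 4 of 4, making B, C, H and S each estimable under additivity. With one center per arm, the before-and-after model would have 10 cells and rank 10, again with 0 residual degrees of freedom, so level effects would still be confounded with center-specific change.

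**The case against.** The strongest reply is that differential impact can mean a comparison of the three added levels with one another, and Step 2 shows that those differences are estimable if the bundle is common. There is text in favor of a common bundle: Table 1 lists the individual and interpersonal levels for all three arms, Study Strengths says all interventions work through couple health education, and all delivery staff received one guide. The special day is men-only ("access will be reserved exclusively for men, including those who are not on treatment for HIV"), but it takes place once a month, which does not rule out couples counseling on other days. A reader might infer from Step 4 that the bundle certainly differs between arms; the documents do not support that. They are inconsistent, and a condensed table may simply leave an item out. This part of the reply stands. It does not rescue the stated comparison with individual and interpersonal activities alone, which fails even when the bundle is identical.

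A second reply is that usual services may already contain the bundle, in which case each contrast with control would isolate the added level. The educational tools build on national couples-counseling standards, and before the intervention partners were already being invited for testing and counseling. But the article never says that the control center delivers the bundle. It presents these activities as part of the interventions, says messages on masculinity were added to the standards, and says partner activities with this goal had never been tested in the program.

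A third reply is that the phrase refers to past studies. No external comparison or data source is described.

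Finally, the stated conclusions concern whole interventions: the article aims to identify the best one, and that does not require separating levels. This stands and limits the consequence.

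**Conclusion.** The point holds as a matter of identification. The increment of the community, health-system or structural level over the shared activities cannot be estimated from these four centers (rank 3 for 4 parameters), whatever the sample size or analysis model. This rests on usual services not containing the same bundle, which no section states. Comparisons among the added levels need three conditions: identical delivery of the shared activities, additive effects, and center differences set aside. The text leaves the first unsettled, and one non-randomized center per arm gives no means of checking the third.

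Two stronger readings should be resisted. A reader might infer that a benefit produced wholly by shared education would be credited to one particular level. It would instead give equal contrasts in all three arms and so no differential impact, and no section says how such a result would be attributed. A reader might also infer that the article presents separation of levels as a main strength. The sentence does stand under Study Strengths, but the strengths named there are the theoretical framework and the real-life setting.

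The outcomes, tests and package-versus-usual-services comparisons are unaffected. What changes is what may be concluded from them, and for that reason the text should be corrected.

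**What to change.** 1. In Outcomes and Statistical Methods and in Study Strengths, replace the level-specific claims with wording such as: each contrast estimates the effect of the whole package delivered at that center compared with usual services; the contributions of single ecological levels are not separable.
2. Reconcile Strategy of the Study, Table 1, the descriptions of the arms under Interventions, and Study Strengths on which arms deliver individual education and which deliver couples education.
3. Tabulate delivery of these shared components by arm (women and couples reached) next to the results. The listed indicators cover part of this: counseling sessions for nudge, services received for special day, and meetings and participants for male champions. Couples counseling is not counted for the last two.

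The cost is wording, a count of counseling sessions in two arms, and a less ambitious claim. No new arm is requested; Step 6 shows that one extra center would not remove the confounding with center.

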**Male champions (community level)**
Number of meetings in the communitiesDuration of meetingsNumber of participants in each meetingQualitative report of male champions on each meeting (qualitative data)
**Special day (health-system level)**
Number of men attending the special dayBasic data on men attending the special day:Employment statusFamily statusLevel of satisfaction of the interventionNumber of partners of women accessing the health facilitysNumber of men receiving services offered during the special day (HIV test and counseling; blood pressure measurement; blood glucose; nutrition; health talks; drama)
**Nudge (structural level)**
Number of couples eligible for interventionNumber of incentives and counseling sessions delivered

## Results

The enrollment of patients in the preintervention phase started in July 2019 and ended on March 31, 2020. There is an ongoing analysis of preliminary data collected at the 4 centers during the preintervention phase. In total, 452 female participants were enrolled in the preintervention phase, with the following distribution: Namandanje (n=133); Kapeni (n=78); Kapire (n=75); and Balaka (n=166). Several meetings have been performed at the centers to organize the intervention phase. As of August 1, 2020, the interventions were initiated at the 3 centers and by September 2020 were ongoing.

## Discussion

### Study Strengths

This study aims to assess interventions targeted at enhancing the involvement of males in women antenatal health care in Malawi. Male involvement in prenatal care is still one of the lowest in the world in Malawi, ranging from 3.2% to 23% [27]. There are multiple reasons for the limited role of male partners in women’s health initiatives. Instead of addressing singular factors supposed to directly cause limited male involvement, the approach of our study is based on an ecological model [17]. The decision to base interventions on a theoretical framework is one of the strengths of this study. In fact, a theory-based approach allows us to better understand the reasons for failure or success of an intervention, develop better strategies, and evaluate their external validity [16,50]. In particular, the ecological model was chosen for this study because it considers not only the beneficiaries (HIV-positive women and their partners) and ART adherence as done in other studies [15] but also the social context that can facilitate or hinder the adoption of healthy practices, namely retention in care and adherence to therapy for HIV PMTCT. All the interventions being evaluated act on individual and interpersonal elements, through couple health education. In addition, each intervention addresses other elements such as the health structure, the community, or the structural level linked to transportation costs. This design allows us to understand how the different levels affect behaviors within the target group and, therefore, health outcomes. Another strength of these interventions is the implementation of these activities in a real-life setting, with the use of personnel already active in the center. This is a significant strength of this study, as it provides reproducible information to other sites.

### Limitations

The study design has some limitations. First, the nonrandomized assignment of the interventions based on feasibility criteria could be a possible selection bias. All patients were enrolled in a high-quality program delivered by an international nongovernmental organization, and the results could be different in other settings such as public health facilities. Second, the interventions are designed based on evaluations conducted in different countries and in a potentially different context. This poses the question of their applicability to the Malawian context. Third, the number of studies conducted on male involvement in Malawi is limited and, in many cases, outdated, which do not allow us to have current data at hand on male involvement in Malawi to compare with our ongoing analysis.

If the study is successful in identifying an effective intervention that enhances male involvement and reduces attrition of HIV-positive women in Malawi, then the resulting strategy can be implemented in many other sites in the country as well as in other countries. The results of the study will be shared with local and central health institutions in the country to disseminate our study findings and enhance good practices fostering improved outcomes for families living with HIV.

